### Outcome measures

There are a range of outcomes measures that will be collected during phases I and II. They are classified as either.Feasibility outcome measures of trial processes, resource use, and management systems (see Table 3), orImplementation outcome measures and determinants of implementation (see Table 3), orPatient-level clinical trial outcomes (see Table 4).

The feasibility outcome measures capture different aspects of the processes, resource use, and management required to run a large-scale implementation trial. For example, data on the processes include screen failures and reason for potential participants declining to be involved in phase II of the trial. Data on resource use include the number of times the digital devices did not work or needed to be repaired. They also include data on the amount of training the physiotherapist required. Data on management includes the number of digital devices from which dosage data were successfully retrieved, and who collected what data.

The feasibility outcome measures also capture patient- and implementation measures of feasibility during both phase I and phase II. These include measures such as patient safety, treatment fidelity, and the success of the implementation strategies in improving physiotherapists’ capabilities, opportunities, and motivation to use the digital devices.

Where appropriate, feasibility criteria have been specified for each outcome measure to guide any modifications required to the study design, implementation strategies and intervention for the proposed large-scale implementation trial (see Table 3).

**Table 3 Tab3:** Feasibility outcome measures

Feasibility outcome measures	Details	Feasibility criteria
1. Processes		
a. Recruitment rate	Number of participants recruited into the study per week (a **PRIMARY** outcome)	Nil
b. Eligibility criteria	Proportion of patients screened who were eligible and ineligible, and reasons why patients were ineligible	Nil
b. Refusal rate	Proportion of people screened who were eligible who declined taking part in the study and the reasons why they declined	Nil
d. Retention rate	Number of participants who have a 3-week assessment (primary outcome timepoint) completed prior to discharge between 2 and 4 weeks post-randomization)	≥ 85% completed for all outcome measures except activity monitor (≥ 80%)
2. Resource use		
a. Equipment	•Number and cost of devices + consumables/support equipment (e.g., data cards) •Number lost/broken devices needing replacement	Nil
b. IT	How many times devices did not work, time needed to fix, how and who it was fixed by and cost of fixing it	≥ 75% devices work for at least 75% of trial time
c. Staff	•Total FTE staff within the physiotherapy rehabilitation team that are participating in the trial •Number of physiotherapists needed training over course of project and number of hours spent training them in using digital devices •Number of physiotherapy students who required training (total blocks and total students) over course of project and number of hours spent training them in using digital devices •Number of training sessions missed by staff and students and reasons why •Number of staff trained and conducting screening, recruitment and outcome assessments	Nil
d. Training physiotherapists to embed digital devices	•Time and hours spent by clinical champion and study investigators in staff training •Number of workshops/journal clubs/clinical reasoning/audit and feedback activities performed	Nil
3.Management		
a. Dosage	•Percentage of exercise practice sheets reflecting usual care and digital device that are complete and legible with repetitions recorded (a **PRIMARY **outcome) •Number of devices that dosage data were successfully retrieved from •Who collected and how were dosage data collected for technology use?	•Exercise practice sheets complete for ≥ 85% of all participants
4. Patient- and implementation outcome measures		
a. Safety	•Number and type of minor and serious adverse events (e.g., falls) and circumstances of event when using digital devices during supervised/semi-supervised/out of therapy practice collected from hospital incidence reporting system	Nil
b. Estimation of effectiveness	•Between group difference and 95% CI for each patient-level outcome measure at 3 weeks post-randomization (these are outlined in Table 4)	Nil
c. Success of implementation	•Fidelity: average total active time in minutes per day using digital devices for mobility tasks (a **PRIMARY** outcome) •Number of days over 3-week intervention technology not used by participants and reasons why (e.g., patient refusal, technology not working, staff shortages) •Device use: percentage of participants each device was used with; average number of different devices used per participant; percentage of devices used per participant where it was progressed (e.g., game level, repetitions, sets, time) •Type of practice: percentage of participants each mobility limitation was trained with devices; average number of different mobility limitations trained per participant •Percentage of staff trained that participated in prescribing and delivering rehabilitation using digital devices	Average of ≥ 30 min per day for > 50% intervention participants; 0 min per day for > 90% control participants (to confirm no contamination)
d. Determinants of implementation success	•Change in physiotherapists’ capability, opportunity and motivation to prescribing and delivering rehabilitation using digital devices, measured using study specific questionnaire (see Additional file 4), developed based upon the COM-B self-evaluation questionnaire [27]	Nil

The patient-level clinical trial outcomes include all the outcome measures that would be used in the future large-scale implementation trial. They are being collected at baseline and 3 weeks after randomization during phase II. If a patient is discharged before the scheduled 3-week assessment, every attempt will be made to collect all the patient-level measures prior to their discharge. The purposes of collecting these data are to ensure they are all suitable outcome measures for the future large-scale implementation trial and that they are all feasible to collect as well as to estimate the impact of the approach taken to guide future sample size calculations. They include measures of mobility, general health and function, quality of life, and physical activity. In addition, data on falls and adverse events will be collected over the 3-week intervention period (see Table 4).

**Table 4 Tab4:** List of patient-level clinical trial outcome measures collected during phase II. These data will be collected at baseline (pre) and 3 weeks (post) for all patient-participants

Outcomes	Pre	Post
Mobility		
1. Short Physical Performance Battery (SPPB) continuous score, 0–3 [28]: measures time taken to complete tasks of gait speed, standing balance, and standing up and sitting down; higher score indicates better mobility	Y	Y
2. Short Physical Performance Battery (SPPB) total score, 0–12 and subscales [29–32]; measures mobility; higher score indicates better mobility	Y	Y
3. Single leg stance: measures standing time on most affected leg in 0–10 s; higher scores indicate better balance	Y	Y
4. Maximal balance range test [33]: measures distance reached forward in millimetres; higher score indicate better balance	Y	Y
5. Step test [34]: measures number of steps in 15 s on each leg, higher score indicates better balance	Y	Y
General health and function	Y	N
6. Functional Co-morbidity Index [35]: collects information on 26 comorbidities and any other the patient reports	Y	Y
7. Technology exposure survey: collects number and frequency of usage of digital devices by Patient-participants before and during the trial	Y	Y
8. Activity Measure for Post-Acute Care (AM-PAC) [36] short form, 0–24 points; self-reported measures of basic mobility; higher score indicates more independence		
Quality of life		
9. European quality of life 5-dimension subscale score (EQ5D-5L) [37], 0–5 points; consists of the EQ-5D descriptive system that comprises 5 dimensions of health and the EQ visual analogue scale (EQ VAS) which records the patient’s self-rated health on a 0–100 visual analogue scale; higher score indicates better quality of life	Y	Y
Physical activity		
10. Average steps per day measured over a 3-day period (1 day at baseline) using the StepWatch activity monitor [38]; higher stepcount indicates greater physical activity	Y	Y
Falls		
11. Falls and fall related injuries from hospital incident reporting system: number of falls	N	Y
Adverse events (intervention group only)		
12. Number of adverse events and details. An adverse event (minor and serious) is defined as an unwanted and usually harmful outcome occurring while the person is participating in the intervention, i.e., whilst undertaking rehabilitation using digital devices (e.g., a fall while using digital devices with no or minor injury (minor AE) or serious injury such as a fracture ( serious AE).	N	Y

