We undertook a clinical trial (*n* = 300) using digital devices to provide exercises in rehabilitation. This trial was called The Activity and MObility UsiNg Technology (AMOUNT) rehabilitation trial. We demonstrated clinically important improvements in mobility from baseline to 3 weeks and 6 months in people using digital devices for mobility exercises and overall physical activity in addition to their usual rehabilitation care [9]. Mobility exercises included standing up from a chair, stepping in different directions, and weight shift in standing while playing games using virtual reality or following a digital exercise program.The digital devices were prescribed by a physiotherapist and the prescription was tailored based on patients’ mobility limitations and preferences. The core element of the intervention was 30–60 min of additional task-specific mobility activities 5 days per week using a range of digital devices to enable tailoring and progression. The digital devices included virtual reality gaming systems, tablet and smartphone applications, and wearable devices. Importantly, the participants enjoyed using the digital devices and most rated the devices highly in measures of usability [9].

Although the first trial, the AMOUNT rehabilitation trial, was a pragmatic trial undertaken in “real-world” clinical settings, the exercises with digital devices provided as part of the intervention were delivered by physiotherapists employed using study funds. To take implementation of this approach to the next level, we need to determine if physiotherapists employed by hospitals can provide exercises using digital devices in addition to their usual therapy and whether devices used in this way improve mobility outcomes. Therefore, we will conduct a feasibility hybrid type II randomized controlled trial [10, 11]. This trial design will enable us to test trial processes to guide the design of a future large-scale implementation trial, pilot strategies to encourage and support physiotherapists to use digital devices as part of their therapy sessions and explore effects of our approach on implementation and patient outcomes. The exercises prescribed with the digital devices will be performed either under the direct supervision of a physiotherapist, as part of a class or in a semi-supervised environment. The digital devices will also provide a way of encouraging patients to practice on their own if deemed safe to do so by their physiotherapist.

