### Participants

There are two participant groups, namely, the therapist-participants who will be supported and encouraged to use the digital devices with their patients through a range of implementation strategies, and the patient-participants who will use the digital devices as part of the therapy provided to them by the physiotherapists. The therapist-participants will be included in Phases I and II, and the patient-participants will be included in phase II. It is not possible to blind either participant group due to the nature of the intervention and implementation strategies.

Therapists will be eligible to participate in phases I and II if they.1.Are physiotherapists who work at the Prince of Wales hospital2. Are employed full-time or part-time and are permanent or casual, or rotate through the rehabilitation ward during the study period.

University physiotherapy students will not be included as participants in either phase I or II, but they may assist in the delivery of the clinical intervention in phase II under the supervision of physiotherapists enrolled in the study. The students will also be provided with education and training in the use of devices within their first week of placements.

Patients will be eligible to participate in phase II if they1. Are admitted to the general rehabilitation ward of Prince of Wales hospital and are at least 18 years old2. Have reduced mobility (Short Physical Performance Battery (SPPB) score of less than 12)3. Are deemed by a clinician to have the potential to improve their mobility4. Have a likely life expectancy of more than 6 months5. Have an anticipated length of stay of ≥ 21 days after the date of randomisation

Patients will be ineligible to participate in phase II if they1. Have cognitive impairment (Mini Mental State Examination (MMSE) [15] < 24 or Montreal Cognitive Assessment (MoCA) [16] < 18) unless their caregiver is present, and willing and able to use digital devices with the patient2. Have insufficient English language skills to participate in the intervention without an interpreter3. Have inadequate vision to use the digital devices4. Have a medical condition(s) precluding exercise (e.g., unstable cardiac disease, uncontrolled hypertension, uncontrolled metabolic diseases, large abdominal aortic aneurysm, or a weight-bearing restriction).5. Inability to balance safely in standing despite the assistance of a staff member or the nominated support person or walking aid.

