
The exercises provided using digital devices to the intervention participants will be documented in a second set of exercise practice sheets designed specifically to capture the trial intervention. The exercises will be documented by the physiotherapist or physiotherapy assistant/student. Like the exercise practice sheets for usual care, the exercise practice sheets for the intervention will also have space to document the type and number of repetitions of each exercise and the active time spent on each exercise. If participants are capable of doing exercises independently, they will be encouraged to document them in their exercise practice sheets.

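### The only source named for adverse events is the hospital incident reporting system, which may under-record minor events and events during unsupervised device practice

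*Protocol article*

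**What the plan says.** All references are to the protocol article.

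- **Source.** Table 3, row 4a (Safety) covers "Number and type of minor and serious adverse events (e.g., falls" and the like, and gives their origin: "circumstances of event when using digital devices during supervised/semi-supervised/out of therapy practice collected from hospital incidence reporting system". The feasibility criterion for the row is Nil.
- **Definition.** Table 4, item 12 states: "An adverse event (minor and serious) is defined as an unwanted and usually harmful outcome occurring while the person is participating in the intervention". Nothing in it requires the event to be witnessed or to be a reportable incident. The item's example of a minor event is "a fall while using digital devices with no or minor injury (minor AE", and its example of a serious event is a fracture from a fall.
- **Group.** The heading above item 12 is "Adverse events (intervention group only". The item names no source of its own. Item 11, on falls, names the incident system.
- **Setting.** The Introduction says that the devices will "provide a way of encouraging patients to practice on their own", where the physiotherapist considers this safe. The intervention section adds that devices may be used outside formal sessions and that exercises may not need direct help from a physiotherapist, family or others.
- **Practice sheet.** The device practice sheet is described as having "space to document the type and number of repetitions of each exercise and the active time spent on each exercise". No event entry is described.

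**The concern.** The definition and the named source do not match well. The definition takes in any unwanted, usually harmful outcome during device use, however slight. The source depends on a member of staff learning of the event, regarding it as an incident and entering it. Two kinds of event within the definition are exposed: minor events that nobody thinks worth an incident report, and events when the patient practises alone or with family. Row 4a expressly includes out-of-therapy practice, which is where this source sees least.

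What is at stake is how the safety result can be read. The outcome measures section says that the patient-level outcomes are those intended for the large trial, and that they are collected here to check that they are suitable and feasible to collect. Adverse events are on that list, so the way they are ascertained is itself being piloted. With a single passive source, the pilot cannot tell few events from few reports.

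**Working it through.** The plan gives no adverse event rate and no capture rate for the incident system, so there is no figure to reproduce. The check has two parts.

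**1. Passages set side by side**

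| Feature | What the article states | Place |
|---|---|---|
| Severity covered | Minor and serious | Table 3 row 4a; Table 4 item 12 |
| Settings covered | Supervised, semi-supervised, out of therapy | Table 3 row 4a |
| Practice alone | Encouraged if judged safe | Introduction |
| Source | Incident reporting system | Table 3 row 4a |
| Second source | None named | Searched wherever adverse events, falls or practice sheets are mentioned |
| Control count | None (intervention group only) | Table 4 item 12 |

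If the source captures a fraction c of events and c is below 1, the count is too low. That direction follows for any such c. The size depends wholly on c, which the documents do not give.

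**2. Illustration with assumed capture**

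Input from the document: n = 15 intervention patients (Sample size, Phase II). Assumption: each affected patient is recorded with probability c.

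*Upper bound when no event is recorded.* The one-sided 95% bound on the recorded share is 1 − 0.05^(1/15) = 0.181. Dividing by c gives the bound on the true share.

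*Chance of recording no affected patient.* With an assumed true risk of 20% per patient, this is (1 − 0.20 × c)^15.

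| Assumed c | Upper bound, zero recorded | Chance of recording none (true risk 20%) |
|---|---|---|
| 1.00 | 18.1% | 3.5% |
| 0.90 | 20.1% | 5.1% |
| 0.75 | 24.1% | 8.7% |
| 0.50 | 36.2% | 20.6% |
| 0.25 | 72.4% | 46.3% |

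*A fixed number of events.* With an assumed 3 true events captured independently, the chance that none is recorded is (1 − c)^3:

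- c = 0.20: 0.512, or 51%
- c = 0.30: 0.343, or 34%
- c = 0.50: 0.125, or 13%
- c = 0.75: 0.016, or 1.6%
- c = 0.90: 0.001, or 0.1%

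At high capture the problem almost disappears; at low capture an empty safety table says little. Nothing in the document shows which case applies.

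**The case against.** The strongest case against has five parts.

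- **The article is a summary.** Table 4, item 12 names no source, and the full protocol and the forms are not shown. A reader might infer that the incident system is the sole source, that the practice sheet has no event field, or that nobody asks the patient at 3 weeks. The documents do not support these as facts. They show only that no other source is named and that no event field or question is described. This stands, and the point is worded accordingly.
- **The examples are falls.** Row 4a and item 12 both illustrate events with falls, which item 11 expects the incident system to record. A reader might infer that many events will be missed, but no figure supports that. This also stands. Falls are given only as examples, however, and an unwitnessed fall without injury during solo practice could still go unreported.
- **Risk is limited by design.** Patients who "Have a medical condition(s) precluding exercise (e.g., unstable cardiac disease, uncontrolled hypertension, uncontrolled metabolic diseases" are excluded, and solo practice needs the physiotherapist's agreement. Citing that exclusion as evidence that symptoms will occur would be wrong, because it removes those patients. This bears on how often events happen, not on how completely they are recorded.
- **Little depends on the count.** Safety is not one of the three primary outcomes and has no criterion. With events counted in one group only, under-recording biases no between-group comparison. The article nowhere says that a low count would be taken as reassurance. This stands and limits the importance of the point.
- **The remedy touches a primary outcome.** Completeness of practice sheets is tested against ≥85%, and the Discussion names accurate recording as a limitation. A new compulsory field could change that result. This stands, and the fix has to deal with it.

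What the objection does not remove is that the article does state a source, applies it to minor and out-of-therapy events, and names nothing beside it. That is a stated choice, not a detail left out.

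**Conclusion.** The point holds as a limited one. The named source is passive and narrower than the definition it serves, so minor events and events in unsupervised practice may be under-recorded. The consequence is confined to an absolute count in 15 intervention patients: a low or zero count could not be read as evidence of safety, or as showing that capture is adequate for the large trial. No control count exists to help interpret it.

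The amount of under-recording cannot be computed from the documents. The figures above rest on assumed capture fractions, an assumed 20% risk or an assumed 3 events, and they run from negligible to serious across that range. The conclusion also assumes that the full protocol names no further source. No contradiction or analysis error is shown. This is an optional, cheap improvement.

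**What to change.** Amend Table 3, row 4a and Table 4, item 12 together. Keep the incident reporting system and add two sources:

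1. A yes/no event line, with room for brief detail, on the existing device practice sheet, including sheets that patients fill in themselves. State that this line does not count towards the ≥85% completeness criterion, so the primary outcome is unchanged.
2. One standard question to intervention participants about events since randomisation, at the existing 3-week contact (or before discharge if that comes first). Ask it after the blinded measures and by existing unblinded study or ward staff, so that the assessor stays blinded.

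Report events by source, so that the pilot shows what each source adds. If the full protocol already names such sources, it is enough to cite them in these two rows.

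The cost is one line on an existing form and one question at an existing visit. The planned minimum is 15 patients × 5 days × 3 weeks = 225 patient-days of device practice, for which a sheet entry is already expected. The downsides are slightly more recording by therapists and patients on a form whose completion is itself being tested, and a possibly higher count of minor events.

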### Primary outcomes

The primary outcome measures are three of the key feasibility outcome measures that are deemed most important for determining the feasibility of conducting a future large-scale implementation trial. They will be collected during phase II from the study records and are described below.Management: dosage

Data will be collected to reflect how well the physiotherapists document the dosage of exercises provided both as part of usual care (both groups) and as part of the intervention (exercises prescribed with digital devices to the intervention group). The exercise practice sheets will be audited for both completeness and legibility, and the results presented as percentages.b.Processes: recruitment rate

This will be measured in terms of number of participants recruited per week (compared to the number screened).c.Success of implementation: fidelity

Data will be collected to capture the fidelity of using digital devices to prescribe appropriate exercises. That is, to determine whether the participants engaged in additional repetitious practice and if so, to quantify the amount of time spent in additional repetitious practice. This will be determined by measuring the average total active time in minutes per day using digital devices for mobility training. These data will be captured in the intervention group exercise practice sheets (and the control group practice sheet to check if any contamination has occurred) (see Table 3).

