The primary aim of this study is to determine the feasibility of conducting a large-scale implementation trial. Specifically, we will determine the feasibility of the following:Collecting dosage data on the amount of repetitive task-specific practice patients receive as part of therapy;Recruiting participants in the trial;Fidelity to the protocol for using digital devices to prescribe appropriate exercises. Specifically, whether physiotherapists can provide 30–60 min of extra therapy on top of usual care using an array of digital devices appropriate for enhancing mobility.

The secondary aims are to:Determine the processes, resource use and management systems required to enable the conduct of a large-scale implementation trialExplore impacts on patient-level outcomes to guide the future trialExplore implementation outcomes and determinants on implementation success in terms of physiotherapists’ capability, opportunity, and motivation to implement digital devices in rehabilitation.

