#### Details of the interventions provided to both patient groups during phase II

### Usual care

Patient-participants in both the intervention and control groups of phase II will receive usual inpatient rehabilitation care. All participants will be assessed by a physiotherapist who will prescribe a series of task-specific exercises to be performed as many times as possible according to their impairments and activity limitations (e.g., practice of standing up or stepping). The conduct of these exercises will be supervised by a physiotherapist, a physiotherapy assistant or physiotherapy student under the overall supervision of a physiotherapist, or by a family member who is educated by a physiotherapist to do so. As is standard practice, the exercises will be individually tailored and progressed. Participants will also receive feedback about their performance, and the exercises will focus on functionally relevant goals. The feedback will be provided in the form of knowledge of performance (e.g., centre of mass movement while shifting weight in standing during game play) and knowledge of results (e.g., game score) Participants will also receive assessment and management by other members of the multidisciplinary team as required. The exercises provided during usual care will be documented by the physiotherapist or physiotherapy assistant/student in an exercise practice sheet. The exercise practice sheet will have space to document details about the type of each exercise, number of repetitions of each exercise, and the active time spent on each exercise. If participants can exercise independently, they will be encouraged to also document this in their exercise practice sheets.

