### Rehabilitation using digital devices (intervention)

Patient-participants randomized to the intervention group of phase II will receive individualized therapy utilising digital devices to enhance mobility and overall physical activity in addition to their usual care. The selection of digital devices are similar to that used in the AMOUNT trial [9] and will be the same as intended for the large-scale implementation trial in the future. Digital devices will be selected according to an intervention protocol that matches different exercises on different devices to common mobility limitations, as well as the physiotherapist considering participant impairments (e.g., upper limb weakness), goals and device preferences (See Additional file 2). The digital devices include rehabilitation and recreation virtual reality gaming systems, tablet and smartphone applications, and wearable devices. Each device provides feedback about task performance, enables individualized tailoring and progression of exercise or physical activity, promotes progress towards a functionally relevant goal, and is relatively inexpensive (see Additional file 3).

Physiotherapists responsible for the day-to-day therapy will teach the participants to use the digital devices and develop individualized exercise programs that enable participants to use the digital devices during and/or outside formal therapy sessions according to the participant’s capability, motivation, and goals. The exercises may or may not require the direct assistance of a physiotherapist and/or family members/friends, nursing staff, physiotherapy students or hospital volunteers. The physiotherapists will aim to ensure participants receive an additional 30–60 min of exercise with the digital devices, five or more days per week for 3 weeks. Our previous work has found this amount of additional practice using digital devices to be feasible and enjoyable for patients [9, 17]. Table 1 provides further detail of the intervention using the TIDieR checklist.

**Table 1 Tab1:** TIDieR Checklist describing the clinical intervention

Checklist item	Intervention group	Control group
Brief name	Digitally enabled rehabilitation in addition to usual care	Usual care

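### The fidelity primary outcome counts minutes on digital devices, so meeting its criterion does not by itself show that extra practice was delivered

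*Protocol article*

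**What the plan says.** The Introduction gives the primary aim for fidelity as "whether physiotherapists can provide 30–60 min of extra therapy on top of usual care". The Primary outcomes section, item c, repeats this purpose: the data are "to determine whether the participants engaged in additional repetitious practice" and, if so, to quantify the time. It continues: "This will be determined by measuring the average total active time in minutes per day using digital devices for mobility training".

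Table 3, item 4c, defines the outcome in the same unit, "Fidelity: average total active time in minutes per day using digital devices for mobility tasks", and sets the criterion "Average of ≥ 30 min per day for > 50% intervention participants". A companion criterion requires zero device minutes in more than 90% of controls, as a check on contamination.

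Three other statements bear on the point:

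- The section on the digital-device intervention describes it as additional to usual care, but also says that physiotherapists will build programs that "enable participants to use the digital devices during and/or outside formal therapy sessions".
- The Setting section says that each patient is usually timetabled for an hour of one-to-one therapy in the morning and another in the afternoon.
- The Usual care section says that the practice sheet has room for the "number of repetitions of each exercise, and the active time spent on each exercise". Device exercise goes on a second set of sheets with the same fields.

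The stated uses of the usual-care sheets are the completeness and legibility audit (Table 3, item 3a) and, for controls, the contamination check.

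**The concern.** The stated question is about addition, but the measure records use. A minute on a device is an added minute of practice only if it does not replace a minute of active usual-care exercise. The article allows device exercise inside sessions that are already timetabled, and names no outcome that checks whether usual-care time was maintained in the intervention arm.

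The earlier AMOUNT trial paid for additional physiotherapists. What is unknown here is whether hospital staff with an ordinary caseload can add the time. Staff short of time could still deliver device minutes by doing less of something else, and the outcome as defined would not show it. A met criterion could then be read as evidence that 30–60 min extra is deliverable when some or all of that time was exchanged. Dosage of practice is also named in the Discussion as the likely primary implementation outcome of the future trial, so the distinction carries forward.

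**Working it through.** There is no sample-size or power calculation in the article to reproduce, so the check is direct arithmetic.

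**Inputs from the article.** 15 patients per arm (Sample size, Phase II); criterion of at least 30 device min/day in more than 50% of intervention participants, and 0 min in more than 90% of controls (Table 3, item 4c).

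**Assumptions, not in the article.** The usual-care active time U that a participant would have had; the share f of device time that displaces active usual-care time; the SD of total active minutes per day.

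**1. Number needed to meet the criterion.** 7/15 = 46.7% and 8/15 = 53.3%, so at least 8 of 15. For the control criterion, 13/15 = 86.7% and 14/15 = 93.3%, so at least 14 of 15.

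**2. Net added time.** With D device minutes per day, total active time is U − fD + D. Net added time is (U − fD + D) − U = D(1 − f), and U cancels.

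| D (min/day) | f = 0 | f = 0.5 | f = 1 | Participant reaches 30 device min? |
|---|---|---|---|---|
| 30 | 30 | 15 | 0 | yes, at every f |
| 45 | 45 | 22.5 | 0 | yes, at every f |

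The result is the same for U = 40, 60 or 120. The criterion does not depend on f.

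**3. Do other planned elements detect displacement?**

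- The control criterion looks only at device use in controls.
- The dosage outcome audits whether sheets are complete and legible, not how many minutes they add up to.
- The linear models in the Data management and analysis section, if applied to the fidelity measure, would compare device minutes with a control arm expected to be at 0. That contrast shows device use.

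**4. Precision of a between-arm difference in total active time.** 95% CI half-width = t(0.975, 28) × SD × √(2/15):

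| Assumed SD (min/day) | Half-width (min) |
|---|---|
| 15 | 11.2 |
| 20 | 15.0 |
| 30 | 22.4 |
| 40 | 29.9 |

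An estimated gain of 30 min would have an interval of about 15 to 45 at SD 20 (30 ± 15.0), and about 0 to 60 at SD 40 (30 ± 29.9).

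**5. The criterion and the arm difference are on different scales.** The criterion counts participants; the difference is a mean. If exactly 8 participants averaged 30 min and 7 averaged 0, mean device time would be 8 × 30/15 = 16 min even with no displacement. The two results need to be read side by side.

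**The case against.** The best defence is that device minutes are an ordinary fidelity measure. The intervention is defined as additional to usual care, usual care is prescribed and recorded separately in both arms, and device exercise has its own sheets. Replacing usual exercise would depart from the protocol. This stands as a description of intent, and it is why device minutes should be kept. But a separate sheet labels the minutes without verifying that they were added, and to assume that they were is to assume the answer to the aim.

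The plan also has partial checks. Days without device use are recorded with reasons, including staff shortages, and StepWatch steps are compared between arms. Neither measures minutes of practice, and some device exercises, such as weight shift in standing, involve little stepping.

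A reader might infer three stronger things that the article does not support:

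- *That moving 30 of the 120 daily minutes onto devices yields no extra practice.* The 120 min is timetabled time, whereas the outcome is active time, and the article does not say how much of a session is active. Device exercise could fill inactive time and be truly additional. Zero gain needs every device minute to displace an active one (f = 1).
- *That a met criterion would launch the large trial.* The Outcome measures section says that the criteria guide modifications to design, strategy and intervention. They are not a go/no-go gate.
- *That the existing data would clearly separate added from exchanged time.* This depends on an unknown SD. At SD 40 the half-width is about as large as the target.

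**Conclusion.** The point holds as a mismatch between a stated question and the measure fixed to answer it. It is not a detail left to an analysis plan, because the article itself sets both the definition and the criterion. At least 8 of 15 intervention participants can reach 30 device minutes a day while the net added active time of each, at exactly 30 min, lies anywhere between 30 and 0. The position in that range depends on f, about which the article gives no information, so nothing here says that displacement will happen or how large it would be. The claim is that the outcome could not reveal it. The criterion remains sound as a measure of device use; what it cannot carry alone is the conclusion that extra therapy was delivered.

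**What to change.** Keep device minutes and the existing criterion, described as a measure of device use, and state in the Primary outcomes section that meeting it is not alone evidence of extra therapy. Then:

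1. From the sheets already planned, compute usual-care active minutes per day and total active minutes per day (usual-care plus device sheets) in both arms, counting days in the same way in each.
2. Report the between-arm difference in each with a 95% CI, as a displacement check.
3. Base any conclusion that 30–60 min extra was delivered on the estimated difference in total active time, judged with its interval against the 30-min target. A rule that the difference need only exceed zero would not do: with no true gain, the point estimate would be above zero about half the time, and a gain of 1 min would count.
4. Report how often active time was actually filled in, since the completeness measure in Table 3 names only repetitions.

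The cost is a change of wording and a small amount of analysis, with no new data collection. The check depends on active time being recorded by staff who are not blinded, and on sheets whose completeness is itself under test. With 15 per arm it is an estimate with modest precision and should not be presented as a formal test.
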